#### Secondary outcome measures

Survival at discharge and time to discharge. Those that survived to discharge is assessed as: neurologically normal (those who had normal tone and posture, were free from seizures, has established full feed by sucking and have normal neonatal reflexes – rooting, suck, grasp, tonic neck reflex, Moro and stepping reflexes) while neurologically abnormal are those with an abnormal tone and posture, poor suck or any abnormal neonatal reflexes at discharge)Association between the levels of NRBC and NRBC/100WBC with neonatal outcomeCranial USS evidence of ventricular enlargement, parenchymal echogenicity or cystic encephalomalacia.Safety of the medications based on the presence or absence of any adverse event such as:
Hypertension: systolic blood pressure in a neonate which is above 95th percentile for age and sex on three separate occasions;Hypotension: a systolic blood pressure in a neonate which is below the 10th percentile for age and sex on three separate occasionsApnoiec attacksThrombotic events;Polycythemia: venous hematocrit of greater than 65%.Any other adverse effect noted during the hospital stay or follow up.Those with cerebral palsy are further categorized based on features present on standardized neurologic examination, and classified as mild, moderate, or severe, with hemiplegia or diplegia, using the Gross Motor Function Classification System (GMFCS) assessment system.

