7. Seizures	Common, focal or multifocal	Absent or uncommon
8. EEG activity	Low voltage changing to seizure activity	Burst suppression to isoelectric

Presence of ≥1 of these signs in any 3 of the above 8 categories is required for diagnosis

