### Clinical monitoring

All the participants are offered standard care according to the unit protocol for HIE. Fluid and electrolyte balance are maintained, oxygen therapy and other respiratory support modes are provided as necessary. Blood pressure is monitored during drug administrations and subsequently through a non-invasive blood pressure monitoring system. Daily monitoring and assessments are conducted until the 8th day of life using the Thompson’s score [47]. A peak score above 15 predicts a bad outcome, whereas maintaining a score below 10 which becomes 0 at 1 week of age suggests a good prognosis. The following clinical course and baseline characteristics are recorded on a pre-designed proforma: the grade of HIE (moderate or severe), the type of respiratory support needed, the presence of seizures, the time to establishment of full oral feedings through sucking and neurologic examination at discharge; the age at commencement of intervention, place of delivery, sex, gestational age at delivery, birth weight, head circumference, mother’s age, parity and intrapartum events are all recorded.

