### Outcome

The outcome measures are assessed at different periods (Table 3). Full neurological examination is performed at discharge and at specified intervals (6,12,18,24 months) until the age of 2 years to assess for neurodevelopmental impairments using the Malawi Developmental Assessment Tool (MDAT) which has been validated for African children [49]. Another assessment tool that has been validated for the neurological assessment of neonates is the Bayley Scales of Infant and Toddler Development 3rd Edition.

**Table 3 Tab3:** Outcome measures at different time periods

Domain	Outcome measure	Stage of HIE	T_**1**_ Discharge	T_**2**_ 4 months	T_**2**_ 6 months	T_**3**_ 12 months	T_**4**_ 18 months	T_**5**_ 24 months
Survival	Survival or death	X	X	X	X	X	X	X
Neurologic exam at discharge	Neurologically normal or abnormal	X	X					
Cranial Ultrasonography	Cranial USS abnormality	X	X					
Neurologic examination at clinic visits	Malawi Developmental Assessment Tool (MDAT) scores			X	X	X	X	X
Laboratory levels of EPO, NRBC, and NRBC/100 WBC	Levels of NRBC and NRBC/100WBC in relation to outcome	X	X					
Adverse reactions to EPO	Safety of the medications based on the presence or absence of any adverse event		X	X	X	X	X	X
Gross Motor Function Classification System (GMFCS) assessment system	Those with cerebral palsy are further categorized based on features present on standardized neurologic examination using GMFCS			X	X	X	X	X

T_1−_ T_5 -_ The five time periods for assessment; *NRBC* Nucleated red blood cells, *GMFCS* Gross motor function classification system.

(Bayley III) assessment tool. However, MDAT tool was preferred for this study since it takes cognizance of the culturally relevant differences in the neurodevelopmental assessment of African children. The Paediatric neurologist that assesses the neurodevelopmental status of the children will be blinded to the treatment arms.

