### Data and safety monitoring plan

Study data are monitored by the Paediatric Pharmacologist and the Biostatistician who are not involved with the day to day management of the recruited patients. An interim analysis for neonatal outcome is scheduled after 6 months of commencement of study in the absence of documented serious adverse effects. A decision to terminate the trial will be taken by the Paediatric Pharmacologist and the principal investigator.

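### The two discharge categories are not complements: a survivor whose only abnormality is seizures, or incomplete sucking feeds, is neither neurologically normal nor abnormal

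*Protocol article*

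**What the plan says.** The protocol article, under Secondary outcome measures, divides infants who survive to discharge into two groups.

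- Normal: those with "normal tone and posture, were free from seizures, has established full feed by sucking and have normal neonatal reflexes". The reflexes are then listed, and suck is one of them. All criteria must be met.
- Abnormal: "neurologically abnormal are those with an abnormal tone and posture, poor suck or any abnormal neonatal reflexes at discharge".

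Table 3, under Outcome, gives the measure only two values: "Neurologically normal or abnormal". The article has no third category and no rule for an infant who fits neither definition.

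Three other places bear on the point. Specific objectives includes a comparison of neurological outcomes between EPO and routine care in the immediate neonatal period. Clinical monitoring says that the proforma records "the presence of seizures, the time to establishment of full oral feedings through sucking and neurologic examination at discharge". The Data and safety monitoring plan states that "An interim analysis for neonatal outcome is scheduled after 6 months of commencement of study", without defining neonatal outcome further.

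**The concern.** Seizures and full sucking feeds count against an infant in the first definition and are absent from the second. Seizures are not a fringe sign here: Table 2 describes them in moderate HIE as "Common, focal or multifocal".

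An infant in the gap must be either left out or placed in a category by someone's judgement. In both cases the outcome cannot be reproduced from the written rule, and two assessors following the text could report different proportions from the same infants. Judgement may also bring bias. Under Risk of bias, the managing physicians know the treatment while the paediatric neurologist does not, and the article does not say which of them assigns the discharge status. If an unblinded clinician does, a discretionary call is exposed to knowledge of the arm. If a blinded assessor does, the loss is mainly one of consistency.

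There is a further ambiguity. The seizure criterion has no time reference. It could mean no seizure during the whole stay or none around discharge, and the size of the gap depends on which is meant.

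**Working it through.** **Inputs.** Both definitions are under Secondary outcome measures and the two-value scale is in Table 3. Each of six signs is taken as present or absent, which gives 2^6 = 64 patterns.

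| Sign present | Rules out normal? | Makes abnormal? |
|---|---|---|
| Abnormal tone and abnormal posture together | yes | yes |
| Abnormal tone alone, or abnormal posture alone | yes | only on the lenient reading |
| Seizures | yes | no |
| Full sucking feeds not established | yes | no |
| Poor suck | yes | yes |
| Another abnormal reflex | yes | yes |

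**Normal.** All six signs must be absent: 1 pattern.

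**Strict reading (tone and posture must both be abnormal).** A pattern escapes the abnormal definition if suck is adequate, the other reflexes are normal, and tone and posture are not both abnormal. That is 1 × 1 × 3 × 2 × 2 = 12 patterns, where the 3 counts the tone and posture combinations and each 2 is seizures or feeding. Abnormal: 64 − 12 = 52. Neither: 12 − 1 = 11.

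**Lenient reading (either is enough).** Patterns that escape: 1 × 1 × 1 × 2 × 2 = 4. Abnormal: 64 − 4 = 60. Neither: 4 − 1 = 3, namely seizures only, incomplete sucking feeds only, and both together.

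No pattern is both normal and abnormal on either reading. With abnormal redefined as failing any normal criterion, the patterns in neither group fall from 11 or 3 to 0.

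**What the point does not touch.** The sample size rests on the primary composite. With 65% against 0.6 × 65% = 39%, two-sided 5% and 80% power, the usual formula for two proportions without continuity correction gives 57 per arm. Then 57 / 0.90 = 63.3, rounded up to 64 per arm, or 128 in total, as stated. Discharge status does not enter.

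**Leverage of one infant (illustration only).** Assume 64 per arm, and assume that the asphyxia mortality of 31.1–62.8% quoted from Nigerian hospitals applied to each arm up to discharge. Survivors per arm would be 64 × (1 − 0.628) = 24 to 64 × (1 − 0.311) = 44. Moving one infant between categories would then shift that arm's proportion by 1/44 = 2.3 to 1/24 = 4.2 percentage points. How many infants would move is not known.

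**The case against.** The best defence is that the normal definition is a full checklist and Table 3 has two values. Anyone failing the checklist would then naturally be abnormal, and the second definition is only a shortened description. That may well be the intention, and it is the rule recommended here. It is not what the text says, because the second definition lists its own qualifying signs and leaves two of the checklist items out.

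Parts of the defence stand. The tone and posture example depends on reading loose prose strictly. Poor suck is the evident counterpart of incomplete sucking feeds and will catch most such infants, so the feeding gap is narrow. An infant who also has a poor suck or any abnormal reflex is classed as abnormal. After moderate or severe HIE, few infants may have seizures and nothing else, and the true number could be near zero.

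A reader might go further and infer three things that the article does not support:

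- *That injured survivors drop out of the outcome.* No text excludes them. Omission is one possible consequence and discretionary placement is the other.
- *That an effect of EPO on seizures or tone could not show.* Either sign bars an infant from normal, so an effect could appear in the proportion normal. Abnormal tone accompanied by abnormal posture, poor suck or an abnormal reflex counts as abnormal in any case.
- *That this is the main short-term neurological endpoint.* The secondary outcomes are not ranked, and the objective speaks of neurological outcomes in general.

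**Conclusion.** The point holds as an error in a stated definition, not as detail left to an analysis plan: the article gives both definitions and they do not fill the two-value scale that it sets. Isolated seizures are the firm example, because they fall in the gap on every reading. Incomplete sucking feeds with an adequate suck also do, but less often in practice. Isolated abnormal tone or posture does so only on the strict reading.

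The consequence is a secondary outcome that is not reproducible and, depending on who classifies, open to bias. Its size in infants cannot be derived from the article. Any percentage of survivors assumed to be affected would have no basis there, and the per-infant shift shown above rests on borrowed mortality figures. The interim look at neonatal outcome may use this status, but the article does not say so. The correction is worth making because it is cheap and removes the gap completely.

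**What to change.** Under Secondary outcome measures, replace the second definition with a complement: a survivor is neurologically abnormal at discharge if any one of the normal criteria is not met, that is, tone or posture abnormal, the seizure criterion not met, full sucking feeds not established, or any listed reflex abnormal.

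State one time window for the seizure criterion, suited to a status at discharge. Seizures at any time in the stay and seizures continuing at discharge are different outcomes and should not be merged. Under the complement rule, the whole-stay version would make abnormal an infant whose seizures had resolved and whose discharge examination was clean.

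Derive the status by rule from the recorded components, not from an overall judgement.

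The cost is small but not nil. The trial is ongoing, so infants already classified must be reclassified. Seizures, feeding and the discharge examination are on the proforma, though the article does not say that seizure dates are, and the chosen window may need them from the clinical notes. Make and document the change before any comparison by arm. If an interim analysis has already used the status, record which rule was applied.

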### Sample size and power calculation

There was no previous study in our environment describing the efficacy of EPO administration on the outcome of HIE. Furthermore, there is a paucity of recent published data on mortality and neurodevelopmental impairment from perinatal asphyxia in our environment. Mortality rate from asphyxia was reported to be between 31.1 and 62.8% in some hospitals in Nigeria [5, 9, 10, 44]. Since no study reported the prevalence of neurodevelopmental impairment of asphyxiated babies at 2 years of life, we expected that the prevalence of a combination of the outcome of “death and neurodevelopmental impairment” at 2 years of life among moderate/ severe HIE in a resource-poor environment such as Nigeria should be higher than the prevalence of death only (31.1–62.8%). Thus, we assumed that the prevalence of “death and neurodevelopmental impairment at 2 years of life” among moderate/ severe HIE without EPO treatment in Nigeria will be about 65%. Additionally, Zhu et al. [40] in Zhengzhou, China found that 24.6% (*n* = 18/73) of babies who had EPO either died or had neurodevelopmental impairment while 43.8% who had placebo died or had neurodevelopmental impairment, giving a relative risk of 0.62 (95% CI: 0.41–0.94). Similarly, the range of protective relative risk that was reported or assumed by previous studies was between 0.65 to 0.71 [41, 45]. Hence, we utilized the power calculator in Stata version 16 statistical software (Stata Corp, USA) to calculate the minimum sample size to be 128 babies based on the assumption that 65% of infants with moderate/ severe HIE may likely die or develop neurodevelopmental impairment without treatment; assuming a protective relative risk of 0.6, 80% power and 10% loss to follow -up.

We utilized the Sarnat and Sarnat staging [43] of moderate or severe HIE for the recruitment of eligible participants (Table 2).

**Table 2 Tab2:** Sarnat and Sarnat staging [43] of moderate or severe HIE

Category	Moderate HIE	Severe HIE
1. Level of consciousness	Lethargy or obtunded	Stupor or Coma
2. Spontaneous activity	Decreased	Absent
3. Tone	Hypotonia	flaccidity
4. Posture	Distal flexion	Decerebrate state
5. Primitive reflexes		
a. Suck	Weak or biting	Absent
b. Moro reflex	Incomplete	Absent
6. Autonomic nervous system		
a. Pupils	Constricted	Deviated, dilated, or nonreactive to light
b. Heart rate	Bradycardia	Variable heart rate
c. Respirations	Periodic breathing	Apnoea

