### Risk of bias

This is a double-blind randomized control trial. Each participant is allocated into the intervention or control group by simple randomization using randomly generated number cards in sequentially numbered sealed opaque envelopes. The randomization list was created and generated online for the study by the Biostatistician based in South Africa. The outcome assessors (Paediatric Neurologist, Radiologist and the Biostatistician) are blinded to the group allocation during the study period. The managing physicians, however, are not blinded to the intervention drugs.

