### Intervention and procedure

The approach to the management of HIE in our center is supportive care. Therapeutic hypothermia is not available. Supportive care includes maintaining normothermia, fluid, electrolyte and glucose balance, respiratory support with continuous positive airway pressure (CPAP) and oxygen, control of seizures and management of other complications as they arise [46]. During this study, participants randomized into EPO group, receives 1000 IU/kg of Erythropoietin intravenously statim on admission then daily for 5 days. This dose regimen was modified from the pharmacokinetic study by Wu et al. [37] Placebo/ control group receives 2 ml of 0.9% Saline statim on admission then daily for 5 days.

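### The hypertension and hypotension outcomes depend on how many pressure readings an infant has, so the comparison between arms can be biased in either direction

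*Protocol article*

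**What the plan says.** All places are in the protocol article.

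- **Secondary outcome measures.** Safety is judged by "Safety of the medications based on the presence or absence of any adverse event such as" a short list that includes both blood-pressure outcomes. Hypertension is a "systolic blood pressure in a neonate which is above 95th percentile for age and sex on three separate occasions". Hypotension is the mirror rule at the lower limit: "Hypotension: a systolic blood pressure in a neonate which is below the 10th percentile for age and sex on three separate" occasions. Neither rule says how many readings are taken, how far apart the three must be, whether they must be consecutive, or over what period they count. The only bound is that the infant is a neonate. Time to discharge is itself listed as a secondary outcome.
- **Clinical monitoring.** "Blood pressure is monitored during drug administrations and subsequently through a non-invasive blood pressure monitoring system". No frequency or end is given. The Thompson score, in the same section, does have a stated last day (day 8).
- **Intervention and procedure.** Both arms are dosed "statim on admission then daily for 5 days", so the dosing occasions are the same by design.
- **Risk of bias.** "The managing physicians, however, are not blinded to the intervention drugs". The assessors named as blinded there are the neurologist, the radiologist and the biostatistician.
- **Sample size and power calculation.** "Mortality rate from asphyxia was reported to be between 31.1 and 62.8% in some hospitals in Nigeria".

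**The concern.** An ever/never rule that needs three out-of-range occasions is a count against an open-ended number of attempts. Each further reading is another chance to reach three. The rate in an arm thus mixes the infants' pressure with how long and how often they were observed.

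The article itself gives three reasons why observation may differ between arms. Mortality is high and the trial hopes to lower it. Length of stay may change with treatment. And infants are monitored under physicians who know the allocation. Any of these can produce a difference in blood-pressure events when the drug does nothing to pressure, or hide a difference when it does.

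At stake are two of the five specifically named safety outcomes. The primary outcome and the sample size of 128 are not touched.

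**Working it through.** The article states no blood-pressure event rate, so there is no figure to reproduce. The check asks how strongly the printed rule depends on the number of readings, and what that can do to a comparison of arms.

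**Inputs from the article**
- Per-reading probability of being out of range in a reference population: p = 0.10 below the 10th percentile and p = 0.05 above the 95th.
- Events needed: 3.
- Mortality 31.1% to 62.8%.
- Relative risk 0.6 for the primary composite.
- About 5 or 6 dosing occasions, depending on whether the admission dose is counted within the five days.

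**Assumptions (not in the article)**
- Numbers of readings.
- Within-infant correlation, modelled as a normal random effect with ICC 0 or 0.5.
- Control mortality 45%, inside the reported range, and EPO mortality 0.6 × 45% = 27%, which applies the composite relative risk to death.

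**Step 1: dependence on the number of readings.** For independent readings, P(X ≥ 3) = 1 − Σ C(n,k) p^k (1−p)^(n−k), summed over k = 0, 1, 2. For ICC 0.5 the same tail is averaged over the random effect.

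| Readings n | Hypotension, ICC 0 | Hypotension, ICC 0.5 | Hypertension, ICC 0 | Hypertension, ICC 0.5 |
|---|---|---|---|---|
| 6 | 1.6% | 7.5% | 0.2% | 2.9% |
| 10 | 7.0% | 14.3% | 1.2% | 6.2% |
| 20 | 32.3% | 26.0% | 7.5% | 13.0% |
| 30 | 58.9% | 33.5% | 18.8% | 18.0% |
| 60 | 94.7% | 46.3% | 58.3% | 27.8% |

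Correlation flattens the rise but does not remove it.

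**Step 2: survival differs, no drug effect on pressure.** Assume 6 readings in infants who die and 30 in survivors. The arm rate is d × P(6) + (1 − d) × P(30), where d is mortality. For hypotension:
- ICC 0: control 0.45 × 1.6% + 0.55 × 58.9% = 33.1%; EPO 0.27 × 1.6% + 0.73 × 58.9% = 43.4%.
- ICC 0.5: control 0.45 × 7.5% + 0.55 × 33.5% = 21.8%; EPO 0.27 × 7.5% + 0.73 × 33.5% = 26.4%. With 64 infants per arm the gap is about 3 infants (4.7 points × 64).

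**Step 3: let dying infants be hypotensive more often.** Same scenario at ICC 0.5, changing only the per-reading probability in infants who die:

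| Probability in infants who die | Control | EPO |
|---|---|---|
| 0.1 | 21.8% | 26.4% |
| 0.3 | 32.5% | 32.9% |
| 0.4 | 38.4% | 36.4% |
| 0.5 | 44.1% | 39.9% |

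The difference vanishes near 0.3 and then reverses. With independent readings the reversal is seen at 0.5 (61.9% v 60.7%).

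**Step 4: let EPO survivors go home sooner.** Assume 42 readings in control survivors, 24 in EPO survivors and 6 in infants who die, with p = 0.10 throughout.
- ICC 0: P(42) = 80.5% and P(24) = 43.6%. Control 0.45 × 1.6% + 0.55 × 80.5% = 45.0%; EPO 0.27 × 1.6% + 0.73 × 43.6% = 32.2%.
- ICC 0.5: P(42) = 39.8% and P(24) = 29.3%. Control 25.2%; EPO 23.4%.

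Steps 2 to 4 all have EPO lowering mortality. In Steps 2 and 4 every reading has the same probability in both arms, and in Step 3 infants who die differ from survivors but identically in both arms. The sign of the difference still changes.

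**The case against.** **Direction.** A reader might infer that the arm with more survivors must collect more events, so that an effective EPO would look harmful. The documents do not support that. It needs survivors to have more readings and dying infants to be no more often out of range at each one. The section on serious adverse events itself links severe pressure disturbance with death, and Steps 3 and 4 show the difference cancelling or reversing. This objection stands in full.

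**Counts.** The definition speaks of occasions, not monitor readings. The scheduled occasions in the article are few: 5 or 6 dosing occasions and daily assessment to day 8. At 6 to 8 occasions the chance rate for hypotension is only 1.6% to 3.8% if independent, or 7.5% to 11.1% at ICC 0.5. Rates at 30 or 60 readings rest on counts that appear nowhere, and the restriction to neonates bounds the period. This stands as a limit on size. It does not remove the dependence, because monitoring goes on after dosing and nothing ties the rule to the scheduled occasions.

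**Percentiles.** A population percentile does not mean that each healthy infant is below it on 10% of readings. Some would almost never cross it and others often. This also stands, and it is why the correlated columns are the more realistic ones.

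**Condensed article.** A full protocol may hold a measurement schedule, and a missing schedule alone would be no finding. What is printed, however, is an operational definition, and it scores the event without reference to any common set of readings.

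**Unequal tails.** The two limits cut off 10% and 5%, and a reader might want them equalised. The inequality makes the two rates non-comparable with each other but does not bias EPO against control. The choice of thresholds is a clinical one, and no change to it is proposed.

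**Conclusion.** The concern holds in this form: the printed hypertension and hypotension events depend on how many readings an infant has. Differences between arms in survival, stay or monitoring under unblinded staff can therefore bias the safety comparison in either direction.

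The dependence follows from the definition and appears under both correlation assumptions. Its effect on the comparison cannot be sized from the article, which gives no reading counts. In the illustrations at ICC 0.5 the spurious hypotension difference runs from about 5 points higher on EPO (21.8% v 26.4%) to about 4 points lower (44.1% v 39.9%). These figures rest on the assumed counts, correlation and mortality. A bias of unknown sign means that neither an excess of events on EPO nor its absence could be read with confidence. This should be corrected, but it does not threaten the primary analysis.

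**What to change.** Keep the two percentile definitions as printed and list every event meeting them, descriptively, over the whole stay. For the comparison between arms, specify:

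1. The data are the systolic readings taken at each study-drug administration after the first dose. These occasions are scheduled identically in both arms.
2. Systolic pressure is compared with a repeated-measures model, and the proportion of readings out of range is reported for each limit.
3. The number of readings per infant is tabulated by arm, so that any difference in observation is visible.
4. Infants who die during the dosing days contribute the readings they have and are also reported separately.

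**Cost.** A short protocol paragraph and, if the values at administration are not already entered, a line on the proforma. No extra measurements are needed.

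**Downside.** Excursions after the dosing days are described but not formally compared. Truncation by early death is reduced, not removed.
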